We will therefore conduct a study that takes these points of criticism into account. The contents of the manual used in this study were derived from a literature analysis and an own preliminary study that has not yet been published. Interventions that require regularity have been replaced. Alternative appointments in parallel groups as well as missing appointments are possible. In the latter case, for compensation subjects can read the content themselves online or watch it as a video.

An exaggerated focus on disturbed sleep is a strong supporting factor of the sleep disorder, which can lead to an intention to force falling asleep and thus prevent falling asleep (attention-intention-effort pathway, [23]). The newly developed manual for shift workers (CBT-I-S) derives its therapeutic rationale from this model: The focus of attention should be shifted away from (the disturbed) sleep and, implicitly, sleep should be improved. To this end, interventions are applied to other factors influencing sleep that have been shown to be relevant in our own preliminary study: depressed mood, anxiety, worrying, rumination, dysfunctional thought patterns and attitudes towards sleep. The interventions used have their primary source in behavioural and positive psychology.

In our preliminary study, attitudes to shift work were another important factor affecting sleep. Cognitive restructuring was used to help participants develop a more positive attitude towards shift work.

Only interventions that have been tried and tested over many years are used, but only from treatment manuals for other disorders. For example: generalised anxiety [24], depression [25, 26], rumination [27], and positive psychology [28].

In addition, psychoeducational material was made available on healthy sleep, sleep disorders and their treatment [4–6, 29–31]. Information on shift work tolerance [32–34] and tips for dealing with shift work [35] were also included in the manual.

The use of these methods is not expected to cause harm to the participants. On the contrary, it is expected that these interventions will have greater positive effects on shift workers than classical CBT-I, because they can be better implemented for this target group.

The aim of the present study is to answer the following research question: Can the new insomnia therapy developed for shift workers (CBT-I-S) improve the sleep of shift workers?

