### {11c}

Participants are motivated to take an active part in the sessions. Attendance is monitored through homework, which is discussed during the sessions, and through the trainers’ assessment of participation in the group.

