### Statistical methods {20 a-c}

For analysing primary and secondary outcomes, we will use linear mixed-models:

We will make within-subject comparisons of the primary and secondary outcomes at the three time points before and after treatment and at follow-up. We will also make between-subject comparisons, i.e., a comparison of the three conditions at the three time points.

Mediator and moderator analyses of the moderation and mediation of the outcomes: No hypotheses about mediators and moderators will be formulated. These analyses are purely exploratory.

We expect low attrition at the post-measurement, but somewhat higher at the follow-up measurement. Individuals who did not complete the post-measurement will be excluded. Those who did not complete only the follow-up may be included in the pre-post comparison but must be excluded from the calculations of the stability of the effects. Depending on their number, it may be necessary to analyse whether they represent a group with specific characteristics. As no post- or follow-up data is expected to be available from the dropouts, an intention-to-treat analysis is not possible. Instead, a per-protocol analysis will be conducted with all participants who were present in at least 4 sessions.

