## Discussion

### Strengths

The study design differs in many ways from other studies on shift work and sleep. First and foremost, the planned sample size of *N* = 142 will give the results more statistical power and thus significance. Due to the online implementation, the acquisition of participants does not have to be limited to the geographical area around the University of Salzburg but can be extended to the entire German-speaking area. In addition, all occupational groups with shift work are included, not just one occupational group, as is the case in many studies. This means that the results can be generalised to all shift workers.

Another strength is the design with two parallel groups: experimental and standard. The effectiveness of the new protocol can be directly compared with standard treatment. The applicability for shift workers and their acceptance can also be determined with this experimental design (drop-outs). Due to the difficulty of recruiting participants, there are several weeks between enrolment and the start of therapy for some participants. Although we do not have an explicit control group, we can still use the ISI data (pre-screening vs. pre-measurement) to check whether there has been spontaneous improvement without intervention.

The development of a specific manual can also be seen as a strength of this trail. Based on literature and the results of a preliminary study, factors that have a significant impact on the sleep of shift workers have been identified. Appropriate interventions were then selected and adapted. All interventions that had to do with regular schedules were removed in order not to jeopardise participant compliance.

However, what is innovative about this treatment manual is the implicit rationale for improving sleep. It is well known that an excessive focus on sleep disturbance can perpetuate the sleep disorder. However, most insomnia therapies focus on the disturbed sleep, thereby increasing the focus on the problem. In our manual, sleep is improved by reducing worry, anxiety, depressive rumination, etc. From the start of therapy, participants understand the key to better sleep: do not think about it and do not try to influence sleep.

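### Intention-to-treat is declared impossible for a reason the protocol itself undercuts, leaving a set selected on attending at least 4 of 7 sessions as the only efficacy population

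*Protocol article*

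**What the plan says.** All of the following is in the protocol article, section Statistical methods {20 a-c}, unless another section is named.

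- The model: "For analysing primary and secondary outcomes, we will use linear mixed-models".
- Missing post-measurement: "Individuals who did not complete the post-measurement will be excluded".
- Missing follow-up only: such participants "may be included in the pre-post comparison but must be excluded from the calculations of the stability of the effects".
- Intention-to-treat: "As no post- or follow-up data is expected to be available from the dropouts, an intention-to-treat analysis is not possible".
- The replacement: "Instead, a per-protocol analysis will be conducted with all participants who were present in at least 4 sessions".

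No other analysis population is named. Section Interventions {11a} gives seven sessions per arm. Missed appointments are allowed in Background and rationale {6}, with this provision: "In the latter case, for compensation subjects can read the content themselves online or watch it as a video". Section {11c} says how attendance is judged: "Attendance is monitored through homework, which is discussed during the sessions, and through the trainers", and the sentence goes on to the trainers' own rating of participation. Blinding {17a-b} states that nobody is blinded. Data collection methods {18a} and {18b} describe online questionnaires, with an e-mail reminder and then a telephone call. Trial design {8} gives the aim as superiority of CBT-I-S over CBT-I.

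**The concern.** Stopping sessions and failing to answer a questionnaire are different events, and the plan treats them as one. Because the outcomes are collected online and chased by e-mail and telephone, someone who leaves the group sessions can still supply t2 and t3. The attendance rule then removes that person for a reason, lack of data, that does not apply.

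Attendance arises after randomisation and may depend on the treatment received. Selecting on it means that the two analysed groups are no longer the two randomised groups. The trial is open-label, and attendance is judged partly by trainers who know the arm. If the standard arm loses the people it did not suit, those who remain look better and a true advantage of CBT-I-S is hidden. If the experimental arm loses its poor responders, superiority can appear where there is none. The superiority claim would rest on this set alone.

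**Working it through.** **1. The plan's own figure.** Inputs from Sample size {14}: f = 0.1, 2 groups, m = 3 times, correlation 0.7, alpha 0.01, power 0.80. For the within-between interaction, λ = f²·N·m/(1 − ρ) = 0.01 × 142 × 3 / 0.3 = 14.2, with df1 = (2 − 1)(3 − 1) = 2 and df2 = (142 − 2)(3 − 1) = 280. Power is 0.803, and 142 is the smallest N that reaches 0.80. The figure reproduces. It is a number analysed, with no allowance for exclusions.

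**2. Whom each rule removes.**
- Neither t2 nor t3: already removed by the post-measurement rule, so the session rule adds nothing.
- t2 missing, t3 present: removed, although a follow-up outcome exists.
- t2 present, t3 missing: kept for pre-post but barred from the stability analysis, although a mixed model can use the record.
- t2 present, fewer than 4 sessions: removed only by the session rule, and the stated reason does not apply. On a literal reading of being present, this includes people who made up four or more sessions by text or video.

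**3. The effect behind N = 142.** Assume a between-arm difference of (0, d, d) SD at t1, t2, t3. Its mean is 2d/3, so the deviations are −2d/3, d/3, d/3, and each arm carries half. Then f² = (1/4) × (4/9 + 1/9 + 1/9)/3 × d² = d²/18, so d = 0.1 × √18 = 0.424 outcome SD.

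**4. Illustrative bias.** Assumed, because the documents give no rates: no true difference; the lowest 15% in one arm and 30% in the other, on a latent attendance score, are excluded; that score correlates r with improvement in both arms.
- The mean latent score of those retained is φ(z)/(1 − p): 0.2332/0.85 = 0.274 for 15%, and 0.3477/0.70 = 0.497 for 30%. The difference is 0.222.
- Bias in SDs of improvement is 0.222 × r = 0.067 / 0.111 / 0.156 for r = 0.3 / 0.5 / 0.7.
- With the protocol's correlation of 0.7, the SD of change is √(2 × 0.3) = 0.775 outcome SD.
- Bias in outcome SD is therefore 0.052 / 0.086 / 0.121.
- Divided by 0.424, this is 12% / 20% / 28%.

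**5. Illustrative type I error.** Simulation with no true effect, 71 per arm, pre-post correlation 0.7, correlation 0.5 between poor response and exclusion, ANCOVA at alpha 0.01, 2000 runs:
- 20% vs 20% excluded: bias about 0, type I error 0.009.
- 10% vs 20%: bias about 0.06 SD, type I error 0.020.
- 10% vs 30%: bias about 0.11 SD, type I error about 0.04.
- 10% vs 40%: bias about 0.16 SD, type I error about 0.06.
- Everyone measured and analysed: bias about 0, type I error 0.008 to 0.011.

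**6. Precision.** With 10% / 20% / 30% excluded (assumed), 126 / 112 / 98 are analysed after rounding down to equal arms, and power falls from 0.803 to 0.74 / 0.67 / 0.59. Where outcomes really are missing, part of this loss would remain under any analysis set.

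**The case against.** The protocol's reason is an expectation about data, and where it proves true a mixed model is no rescue. A participant with t1 only adds little to the treatment contrast, and including such records relies on missing-at-random. This stands. It means that the population must be changed together with continued measurement, and the reminders in {18b} are not restricted to attenders. It does not justify discarding people who did supply data.

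A reader might infer that anyone who makes up a session by text or video is thrown out. The documents do not support that: three of the seven sessions can be missed without removal, and Interventions {11a} arranges two parallel groups per condition so that alternative appointments exist. Only those missing four or more are affected.

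A reader might also infer that the sponsor expects drop-out to differ by arm. It does not say so. Strengths says only: "The applicability for shift workers and their acceptance can also be determined with this experimental design (drop-outs"). Statistical methods expects low attrition at the post-measurement, and the standard arm's sleep restriction was softened to protect compliance. Differential drop-out is a plausible inference from three places: the remark that sleep restriction is hard for shift workers to carry out, the expectation that CBT-I-S can be better implemented, and the use of drop-outs as a marker of acceptance.

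The plan also foresees looking at whether non-completers differ from the rest, but only depending on their number, and that does not restore the comparison.

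Finally, analysis sets can be left to a statistical analysis plan. Here the protocol rules one set out and names another, so this is stated text and not a gap.

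**Conclusion.** The point holds in this form: the reason given does not support ruling out intention-to-treat, and the only named efficacy set selects on post-randomisation attendance in an unblinded superiority trial. The added harm falls on participants who have outcome data but attended fewer than 4 sessions, and on partial records that the model could use.

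The size cannot be derived from the documents. Under the assumed 15% vs 30% exclusion and correlations of 0.3 to 0.7, the bias is about 0.05 to 0.12 outcome SD, or 12 to 28% of 0.42 SD. That comparator itself rests on the (0, d, d) profile. Dividing the improvement-scale bias of 0.067 to 0.156 directly by 0.424 would suggest 16 to 37%, but that mixes two SD scales and overstates the share. The direction depends on which arm loses its poor responders, so the documents do not support saying that the plan favours CBT-I-S. With equal exclusion and the same link to response in both arms, the bias is about zero.

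**What to change.** Replace the sentences on exclusion, intention-to-treat and per-protocol with: *The primary analysis includes all randomised participants in the arm to which they were randomised, using a likelihood-based linear mixed model on all available t1, t2 and t3 data; t2 and t3 questionnaires are requested from everyone regardless of session attendance.*

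Keep participants who miss only t3 in the model. Keep the at-least-4-sessions set as a supplementary analysis, and say whether sessions made up by text or video count towards the four. State that the mixed model relies on missing-at-random; a missing-not-at-random sensitivity analysis is optional.

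The cost is a change of wording, plus reminder e-mails and calls to people who have stopped sessions, through a route that {18b} already provides. The estimated effect may be slightly diluted if non-attenders benefit less.

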## Methods: monitoring

### Data monitoring {21a-b}

We will not set up a Data Monitoring Committee (DMC) as we consider the risks to participants in this study to be minimal. Should any problems arise during the study, participants should contact their trainer or the study management. Based on these reports, the study management will decide whether the study should be modified or cancelled. The final decision will be made by the project supervisor. A formal interim analysis is not planned.

### Harms {22, 30}

Participants are asked to report any problems or impairments they experience as a result of the study to the trainer in their group or directly to the study management. They will be collected and, if necessary, discussed with the project supervisor.

We do not expect any harm to the participants. Should a negative development nevertheless occur in the course of the treatment, we will provide ancillary as well as post-trial care: We will work out possible solutions with the participants and, if necessary, offer alternative treatment options and appropriate contacts.

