### {11b}

The interventions will be stopped or modified if, contrary to expectations, the trainers notice a deterioration in individual participants during the sessions, or if participants contact the study management with complaints.

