### Outcomes {12}

The primary outcome is improvement in the following key sleep variables: total sleep time, sleep onset latency, subjective sleep quality and daytime sleepiness. We also want to measure the severity of the sleep disorder.

Secondary outcomes are improvements in depressive mood and anxiety, dysfunctional sleep attitudes, and cognitive and physiological arousal.

Data will be collected at three time points: before starting treatment, at its end and 6 months later as a follow-up. We will compare group means between groups and within groups at each time point. Since we will have multiple primary outcomes over multiple time points, we will adjust the α-level using a Bonferroni correction.

The magnitude of the differences, especially in the pre-post comparisons, should not only be statistically, but also clinically significant. This means, for example, that subjects no longer meet the criteria for a sleep disorder (DSM-5, [11]) after treatment.

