### Blinding {17a-b}

There is no blinding. Both trainers and participants know which group they are in.

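### Every stated harms route is passive, so reported harms may be incomplete and picked up differently by arm, and the scales that could show worsening are not designated for harms

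*Protocol article*

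**What the plan says.** Four places in the protocol article describe how harm comes to notice.

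- Harms {22, 30} sets the route for participants: "Participants are asked to report any problems or impairments they experience as a result of the study to the trainer in their group". The study management is named as an alternative recipient. On handling: "They will be collected and, if necessary, discussed with the project supervisor". Care is promised both during and after the trial, but the trigger reads "Should a negative development nevertheless occur in the course of the treatment".
- Data monitoring {21a-b}: "Should any problems arise during the study, participants should contact their trainer or the study management". There is no data monitoring committee. The study management decides from these reports whether to change or end the study, and the project supervisor has the final word.
- {11b}: interventions are stopped or changed if "the trainers notice a deterioration in individual participants during the sessions, or if participants contact the study management with complaints".
- Blinding {17a-b}: "Both trainers and participants know which group they are in". Auditing {23} adds that trainers are supervised separately by condition.

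ISI, ESS and HADS-D are completed online in both arms at t1, t2 and t3 (Outcomes {12}, Data collection methods {18a}). Outcomes {12} frames them as improvement: "We will compare group means between groups and within groups at each time point". Statistical methods {20 a-c} excludes people without a post-measurement and analyses those who attended at least four sessions.

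**The concern.** Each harms route needs someone to speak up or a trainer to notice. No scheduled question asks every participant, in the same words and at the same time, whether anything has become worse. The person most likely to hear or see a problem knows the arm, and the supervision around that person is arm-specific, so the chance that a problem is recorded can differ between arms for reasons unrelated to treatment.

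Two consequences follow. First, a low count of reported harms would say little, because a passive system tends to return few reports whatever the true rate. This matters because the article expects no harm and gives these reports as the basis for changing or ending the study. Second, a difference in reports between arms could not be separated from a difference in ascertainment. The arms differ in content (only CBT-I includes sleep restriction), so which arm sees more worsening is a fair question in a superiority trial.

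**Working it through.** **1. The plan's own figure.** Sample size {14}: 2 groups, 3 times, f = 0.1, correlation 0.7, alpha 0.01, power 0.80. For the within-between interaction, lambda = f² × N × m / (1 − rho) = 0.01 × 142 × 3 / 0.3 = 14.2, with df 2 and (142 − 2) × 2 = 280. Power is 0.803 at N = 142 and 0.796 at N = 140, so 142 is reproduced. Equal allocation (Trial design {8}) gives 71 per arm. The article gives no harm rate and no capture rate.

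**2. The reporting routes side by side.**

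| Place | Who must act | Attribution to the study required? |
|---|---|---|
| Harms {22, 30} | participant | yes |
| Data monitoring {21a-b} | participant | no |
| {11b}, complaints | participant | not stated |
| {11b}, observation | unblinded trainer, in a session | no |

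The two main reporting instructions set different thresholds. None of the four is a scheduled enquiry.

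**3. What the scales can and cannot cover.** They are collected on one schedule in both arms and not through the trainer, so worsening among completers can be compared. Three kinds of worsening fall outside them and rest on the passive routes alone: problems outside the scales' domains, worsening that comes and goes between measurement points, and worsening that leads someone to leave. Statistical methods {20 a-c} widens the third gap by dropping those without a post-measurement and those with fewer than four sessions.

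**4. Illustrations.** All capture and worsening rates here are assumptions.

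- Zero reports in one arm of 71, everyone asked: the one-sided 95% upper bound is 1 − 0.05^(1/71) = 4.1%. If only a fraction c of events is reported, the bound on the true rate is that figure divided by c: 8.3% at c = 0.50 and 13.8% at c = 0.30.
- Equal true worsening of 10%, unequal capture: 71 × 0.10 × 0.50 = 3.6 against 71 × 0.10 × 0.25 = 1.8 expected reports, a spurious twofold ratio. At 20% worsening the figures are 7.1 and 3.6. A two-sided 5% test would call these differences significant about 12% and 20% of the time, so the usual result is a misleading count and not a false positive test.
- True worsening of 10% versus 20%, 71 per arm, two-sided 5%, normal approximation. The pooled standard error is √(2 × 0.15 × 0.85 / 71) = 0.0599 and the unpooled one is √((0.09 + 0.16) / 71) = 0.0593. Then z = (0.10 − 1.96 × 0.0599) / 0.0593 = −0.29, giving power of about 38%. If half of events are captured in both arms it is about 20%, and if a quarter, about 12%.

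**The case against.** The other side has substance. Data monitoring {21a-b} asks for any problem without attribution and offers the study management as an alternative to the trainer. A reader of the Harms section alone might infer that a harm is recorded only if the participant blames the study. The article as a whole does not support that; it shows two instructions that disagree.

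A reader might also infer that worsening is missed altogether and cannot be compared. That is too strong, because the online scales allow a comparison among completers. Nor can one say that individual change is ignored: Outcomes {12} gives, as an example of clinical significance, participants no longer meeting diagnostic criteria. That criterion points towards improvement, but it is individual-level. A deterioration table could sit in a full protocol or SAP that is not shown, so its absence from the article is not the point made here.

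Other inferences also go too far. The article does not say that participants have no trainer contact in the six months after treatment. It offers alternative appointments, and attendance is monitored, so it is not established that people who worsen go unseen. The supervisors are experienced and independent of the trial management, which is a safeguard as well as an arm-specific arrangement. The capture rates are invented for illustration, the trial is described as minimal risk, and no relative-safety claim is planned.

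What remains is a stated rule that relies entirely on passive reporting through unblinded people, two reporting thresholds that differ, and an analysis rule that removes those whose worsening the scales are least likely to show.

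**Conclusion.** The point holds in limited form. Spontaneously reported harms may be incomplete and may be ascertained differently by arm, yet they are the stated basis for changing or ending the study. The scheduled scales could partly fill the gap, but the article does not designate them for harms, and the stated exclusions remove non-completers and low attenders.

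This follows from the text and needs no assumption about rates. Its size does: the document gives no capture fraction, so the 8% to 14% bounds and the twofold ratio show only what could happen. The efficacy comparison and N = 142 are untouched. What is weakened is any reading of few reports as evidence of no harm, and any comparison of reported harms between arms. It is an inexpensive improvement worth making, not a fatal flaw.

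**What to change.** 1. In Harms {22, 30} and Data collection methods {18a}: add to the t2 and t3 online questionnaires, identically in both arms, one mandatory item on any new or worsened problem since the last measurement, without asking whether the study caused it. Ask the same item in the reminder call already planned in {18b}. Keep voluntary reports as an additional source.
2. In Statistical methods {20 a-c}: report per arm, for all randomised participants with any post-baseline data regardless of sessions attended, the number whose ISI, ESS or HADS-D worsened by more than a margin the sponsor fixes in advance. Give the number without data beside it.
3. Reconcile Data monitoring {21a-b} with Harms {22, 30} on whether attribution to the study is required. Within Harms {22, 30}, reconcile the trigger tied to the treatment period with the promise of care after the trial. The content of any care rule is for the sponsor.

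Cost: one survey item, one line in the call script, one table and a small protocol amendment, with no extra staff or visits. More events will be recorded, most of them unrelated. Recruitment began in July 2023, so the item covers only measurements taken after it is introduced and should start in both arms at the same time.
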